**FIGURE 3 mpr1980-fig-0003:**
[figure not shown]
Geographical variation in compulsory hospitalised patients in Europe and Norway. Average rates per 100.000 inhabitant. Map based on data from (Hofstad et al., 2021; Sheridan Rains et al., 2019).

There are likely many factors related to the services and their patient populations, that influence the varying rates of compulsory admission. Characteristics of service providers might include bed capacity and duration of hospitalisations (Bale et al., 2021); clinicians' evaluation of decision‐making capacity (Høyer et al., 2022); different attitudes to coercion, which has been shown to vary between professions (Aasland et al., 2018); varying interpretations of legal criteria (Feiring and Ugstad, 2014); availability of systematic family involvement and support for people with SMI (Hestmark et al., 2021); other local experience‐based practises, including quality of voluntary care, which can impact on whether compulsory care is considered necessary (Sharpe, 1997); or other individual differences in clinical decision‐making (Bagby et al., 1991). Variation related to case‐mix might include differing characteristics among the population‐at‐risk of compulsory care, such as age, gender, ethnicity, employment status, comorbidity and previous history of compulsion (Barnett et al., 2019; Walker et al., 2019).

### The geographical lottery

2.6

For people with SMI, the geographical variation produces a lottery‐like situation. In one area, specialists might follow an early compulsory care approach, based on the expectation that admission and/or pharmaceutical treatment is in their best interest, whether they agree or not. In the neighbouring area, specialists may believe that patient autonomy and long‐term therapeutic relationship are more important and are inclined to wait and see if a crisis can be averted or less restrictive interventions can be provided voluntarily.

The care that patients receive based on such idiosyncratic decisions can appear arbitrary and mimics participating in an RCT. Geographical variation in compulsory mental health care thereby enables knowledge production by providing a quasi‐experimental framework which permits causal inference to be drawn from observational registry data. Service providers' preferences can be used as an Instrumental Variable (IV) to estimate the causal effect of a ‘treatment’, such as compulsory care, on various outcomes (Brookhart and Schneeweiss, 2007; Widding‐Havneraas et al., 2021). These data are already being collected in mandatory national registers and cover entire populations, yielding results of high external validity at a low cost.

### Provider preference based instrumental variables as alternative to RCT

2.7

Unmeasured confounding occurs when unobserved factors affect both treatment and outcome. This can overestimate or underestimate treatment effects. Preference‐based IVs can address this problem by exploiting random variation induced by an instrument to isolate exogenous variation and remove confounding variation, resulting in a quasi‐experimental approach that only utilizes exogenous variation to estimate the treatment effect (Angrist et al., 1996; Widding‐Havneraas et al., 2021). Instrumental variable analyses have been shown to produce estimates comparable to those from randomised experiments (Cook et al., 2008; McClellan et al., 1994; Stukel et al., 2007), in contrast to conventional observational studies (Cook et al., 2008).

The use of IV and registry data appears to be a promising way to estimate causal effects of compulsory care, while circumventing the many obstacles that may prevent RCTs and threaten to bias conventional multivariable regression approaches. The data are collected in a naturalistic context and the results will be representative and relevant for clinical practice. Since we can follow people over years, we can also track long term consequences of compulsory care. To the best of our knowledge, this project will be the first to apply this method to help resolve the controversy on the effectiveness of compulsory mental health care (Widding‐Havneraas et al., 2021) and can thereby push the research frontier on a topic of considerable societal importance.

## OBJECTIVES

3

The overarching aim is to determine whether compulsory mental health care results in superior, worse or equivalent health and other outcomes for people with SMI. Norwegian registry data on real‐world practice will provide outcomes and trajectories following compulsory care including emergency care/injuries and cause‐specific mortality; comorbidities and substance abuse; compulsory rehospitalisation or outpatient commitment; labour force participation, welfare reliance and educational attainment; supported housing; and serious violence and victimisation, see Figures 4 and 5. The proposed project is organised in two work packages (WP).

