### Why RCTs are not likely to resolve the controversy

2.3

Conducting RCTs to investigate the effectiveness of compulsory care is challenging due to practical, legal, and ethical considerations. Double‐blinding care status is impossible, leading to bias risks. Strongly opinionated clinicians can hinder clinical equipoise. For financial and practical reasons, RCTs require a short time frame, making them unsuitable for answering questions related to long‐term outcomes over years. Even if these practical constraints could be mitigated, many ethics committee would not approve randomising people who meet legal criteria for compulsion to voluntary status; the English RCT on OC was required to provide a detailed legal opinion prior to approval (Dawson et al., 2011).

Some commentators argue that RCTs may be suboptimal for evaluating the effectiveness of complex interventions such as OC, which operate in open systems involving social actors (Duncan et al., 2020; Mustafa, 2017; O’Reilly and Vingilis, 2018).

Consequently, it remains unclear whether compulsory mental health care is beneficial, either at the individual or societal level, and whether outcomes expected by legislators are actually delivered. This uncertainty, coupled with differing clinician opinions, provides room for considerable practice variation.

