### WP2: Short and long‐term causal effects of compulsory inpatient and outpatient mental health care, including administration of medication without consent

3.2

The main objective of WP2 is to estimate the causal effect of compulsory mental health care on health and social functioning outcomes for people with SMI, potentially including long term costs to the public purse and society associated with these differences. We will use variation in clinical practice among catchment areas as IV to estimate the causal effect of compulsory care on multiple outcomes (see Figure 5). The primary analyses will be restricted to (a) people with SMI; and (b) people who are referred to compulsory inpatient mental health care.

We expect that patients on the margin of compulsory care after discharge will be treated differently depending on whether they live in areas with higher or lower tendency to use OC. Since OC is most often used to ensure medication compliance (Riley et al., 2019) and almost all people on OC receive antipsychotic treatment (Barkhuizen et al., 2020; Riley et al., 2019; Rugkåsa et al., 2015), we will use provider preference for use of OC as a proxy to measure the effect of administration of medication without consent. This WP will also test assumptions that must be fulfiled for IV‐estimates to credibly reflect causal relationships (Widding‐Havneraas et al., 2021).

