### Assumptions of provider‐preference instrumental variables

5.2

First, the *relevance criterion* implies that the instrument must be correlated with the treatment variable. We intend to generate IVs at the regional provider level of catchment area to Community Mental Health Centres (Ruud and Friis, 2021). Stable geographical variations in compulsory hospitalisation between catchment areas have been documented, and more than 80% of variation in ranked rates of compulsory hospitalisation per population could be predicted by the area rankings for the previous year, while 50%–75% of variation in inpatient rates could be predicted this way (Hofstad et al., 2021), suggesting that provider preference for compulsory care can be a strong instrument (Hernán and Robins, 2020).

Second, the *exclusion restriction assumption* implies the instrument should only impact the outcome through treatment. This means that service providers' preferences for using compulsory mental health care in an area should impact whether involuntary care is initiated, while being uncorrelated with outcomes through other paths. We will use a *negative control population* to test this assumption (Lipsitch et al., 2010); since provider preference should have no impact on those who were not in contact with mental health services, the impact of the instrument on the outcome should be zero in the control cohort.

Theoretically, the instrument will control for unobserved and observed characteristics of individuals that can affect the outcome. However, instrument‐outcome confounders can still bias estimates, in which case the instrument would not be equivalent to “as‐good‐as‐random assignment” (Garabedian et al., 2014). So the third *assumption of no confounding* requires that there are no unmeasured common causes of the instrument and the outcome. This will be tested indirectly through balance tests of baseline covariates (Brookhart and Schneeweiss, 2007).

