The fourth assumption of *monotonicity* ensures that the estimand can be interpreted as the Local Average Treatment Effect (LATE). Individuals who clearly fill criteria for compulsory care are assumed to be subject to compulsion in all areas, while persons where compulsory hospitalisation is clearly not indicated are not subject to compulsion anywhere. Consequently, the estimand represents the effect of compulsory care for people with SMI at the margin/in the grey zone of compulsory care; individuals who are expected to be treated differently if they live in areas with a high versus a low use of compulsory care (See Figure 2). By design, we know that all people who are assigned to the treatment (compulsory care), will receive it, thereby ensuring no ‘*defiers’*.

Subject‐matter knowledge, required for all but the first assumption, will be provided by project group members, as well as service‐users and providers. Topics meriting investigation include whether the variation is random or remains stable over time. Are there differences in case mix, with different prevalence of SMI between areas? Is there risk of selection bias, where service users residing in low‐compulsion areas, but require compulsory hospitalisation, are transferred to areas that use more compulsion?

In general, people are unaware whether rates of compulsory mental health care in their catchment area are high or low compared to the country average. Given the retrospective baseline, the quasi‐experimental framework is similar to a double‐blinded experiment where neither service users nor providers could identify the treatment. While some clinicians may have recognised that the use of compulsory care tended to be higher or lower within their area, they were unaware that they partook in a natural experiment. There is also little reason to expect that people self‐selected to areas based on compulsory hospitalisation rates, thereby reducing the risk of selection bias.

Even if the exclusion restriction assumption is violated, the ‘*reduced form’* can provide an unbiased estimate of the effect of the instrument on the outcome (Chernozhukov and Hansen, 2008), and will answer whether a higher or lower propensity for compulsory care results in superior, worse or similar outcomes for patients.

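### Later compulsory readmission and outpatient commitment are listed outcomes not excluded from the area-preference IV analysis, although the same preference decides them directly

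*Protocol article*

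**What the plan says.** - **Outcomes.** Section 3 states a causal aim for people with severe mental illness. Its list of outcomes and trajectories includes "comorbidities and substance abuse; compulsory rehospitalisation or outpatient commitment; labour force participation, welfare reliance and educational attainment". The list is not divided between the two work packages and refers to Figures 4 and 5.
- **Instrument.** Section 3.2 (WP2): "We will use variation in clinical practice among catchment areas as IV to estimate the causal effect of compulsory care on multiple outcomes (see Figure". The reference is to Figure 5. Section 5.2 sets the level: "We intend to generate IVs at the regional provider level of catchment area to Community Mental Health Centres". A second use of area preference concerns OC: "we will use provider preference for use of OC as a proxy to measure the effect of administration of medication without consent". Section 3.2 also expects that, after discharge, marginal patients will be handled differently according to their area's tendency to use OC.
- **Strength of the instrument.** Section 5.2 relies on stability: "more than 80% of variation in ranked rates of compulsory hospitalisation per population could be predicted by the area rankings for the previous year". The same sentence gives 50%–75% for inpatient rates.
- **Exclusion.** Section 5.2 requires that preference reach the outcome only through treatment. The planned test uses a control population with no contact with mental health services. If exclusion fails, the section falls back on the reduced form.
- **Repeated decisions.** The caption of Figure 6 shows compulsion being decided again at several points after referral. Section 5.1 draws the cohort from 2015–2016 and takes data up to 2025.

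**The concern.** A provider-preference instrument works for an outcome only if the preference acts on that outcome through the treatment being studied and by no other route. Later compulsory admission and OC are themselves decisions of the kind that the preference describes. A patient from a high-preference area who comes back into care meets that preference again, whatever the first episode did. The stability that makes the instrument strong is what opens this second route.

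The project could then report that compulsion leads to more compulsion when the earlier episode had no such effect, or even reduced later compulsion. Section 6 (Discussion) says that worse outcomes in high-propensity areas would strongly support reducing compulsion, so an artefact of this kind could feed a policy conclusion. For other outcomes read years later, the estimate combines the effect of the first episode with that of any later compulsion.

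**Working it through.** The article gives no sample size, power or effect figure on this point, so there is nothing to reproduce. The check asks what the IV ratio estimates when the preference persists.

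**Inputs from section 5.2.** The year-to-year correlation rho is the square root of the share of variation predicted:
- inpatient rates: √0.50 = 0.707 and √0.75 = 0.866
- population-based ranks: √0.80 = 0.894 (the article says more than 80%)

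**Assumptions, not in the article.** A share q of patients (0.2, 0.4 or 0.6) reaches a later decision point. The preference acts equally strongly, and in the same direction, at both decisions. The one-year area correlation stands in for the persistence of preference between the two decisions.

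**Formula.** Let Z be the area preference at the first decision, D1 the earlier episode and D2 later compulsion. The Wald estimate is cov(D2, Z) / cov(D1, Z). If D1 has no effect on D2, the numerator is q × rho × (instrument strength) × var(Z) and the denominator is (instrument strength) × var(Z). The ratio is q × rho, where it should be 0.

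**True null effect on later compulsion:**

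| rho | q = 0.2 | q = 0.4 | q = 0.6 |
|---|---|---|---|
| 0.707 | 0.14 | 0.28 | 0.42 |
| 0.866 | 0.17 | 0.35 | 0.52 |
| 0.894 | 0.18 | 0.36 | 0.54 |

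A simulation (75 areas of 1,500 people, sizes chosen only for the check) agreed with q × rho to within 0.01 in these nine cells. With rho = 0 it gave 0.00 to 0.03.

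**True protective effect** (simulation, q = 0.4, rho = 0.894). The earlier episode cancels later compulsion with probability 0.3, 0.5 or 0.8. Without persistence the estimates are −0.06, −0.10 and −0.16. With persistence they become +0.24, +0.17 and +0.05, so the sign reverses.

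**Other long-term outcomes.** If D1 has effect b1 and D2 has effect b2 on outcome Y, the Wald estimate is b1 + b2 × q × rho. With q × rho = 0.4 × 0.894 = 0.358:
- b1 = 0.2, b2 = 0.2: 0.2 + 0.072 = 0.27 (inflated)
- b1 = 0.2, b2 = −0.2: 0.2 − 0.072 = 0.13 (attenuated)
- b1 = 0, b2 = 0.2: 0.07 (spurious)
- b1 = 0.2, b2 = 0: 0.20 (unbiased)

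**Drift over time.** If preference decays yearly as rho^h, the correlation at 5 years is 0.18 (0.707^5) to 0.57 (0.894^5), and at 9 years 0.04 to 0.37. At 5 years the false effect would be 0.2 × 0.18 = 0.04 to 0.6 × 0.57 = 0.34. If preference is a fixed trait of the area, it does not shrink.

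**Safeguards.** People with no service contact never face a readmission or OC decision. They would show a zero association however large the violation, so the negative control cannot detect it. The reduced form estimates the effect of living in a high- or low-propensity area. It does not recover the effect of an episode, and for later compulsion it says little more than that areas preferring compulsion use more of it.

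**The case against.** The strongest reply is that the article does not say that later compulsion will be an IV outcome. The list in section 3 comes before the split into work packages, and descriptive use in WP1 would be harmless. WP2 speaks of health and social functioning, and neither the abstract nor section 2.2 names later compulsion among the outcomes. Figure 5 is not shown, and its caption covers outcomes and/or baseline characteristics. This stands as a limit: a reader might infer that the IV analysis of later compulsion is fixed, and the text does not establish that. But section 3 attaches a causal aim to the list, both sections point to Figure 5, and nothing shown takes these items out of WP2.

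Second, the article never defines treatment as one index episode. If treatment means compulsory exposure over follow-up, later compulsion is part of the exposure and there is no violation. This also stands, and it is one of the two ways to repair the estimand. It does not rescue later compulsion as an outcome, because it would then be exposure and outcome at once.

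Third, part of the remedy is already there. Section 6 frames its scenarios by area propensity, section 5.2 offers the reduced form and lists stability over time as a topic to investigate, and section 3.2 promises tests of the IV assumptions. These help with interpretation, but the stated aim of WP2 remains the effect of compulsory care on people, and the named test of exclusion misses this path.

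A reader might also infer that all long-term effects are inflated, for example by 1 + 5 × 0.4 × 0.894 = 2.8 times over five years. That needs every episode to have the same effect, 40% of patients to re-present each year and no decay in preference. The documents support none of these, and the working shows that attenuation is equally possible.

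**Conclusion.** The point holds in conditional form. If the instrument is applied to the listed outcomes as the text allows, and treatment is an earlier compulsory episode, exclusion fails for later compulsory admission and OC. The estimate is then biased upward: a true null would appear as about +14 to +54 percentage points, and a protective effect could be masked or reversed. Other long-term outcomes are contaminated in a direction that cannot be known beforehand.

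The stability figures come from the article; the share re-presenting (20–60%) and equal instrument strength are assumed. The upward direction also needs the preference to push both decisions the same way. Where the instrument is inpatient preference and the outcome is OC, that is open, since section 3.1 will test whether the two forms go together or replace each other. The bias shrinks if preference decays.

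A secondary matter is the comparison in section 5.2 with a double-blinded experiment "where neither service users nor providers could identify the treatment". Legal status is known to patients and clinicians, and section 2.3 says that double-blinding "care status is impossible, leading to bias risks". A reader might infer a flat contradiction. The context in section 5.2 is unawareness of the area's rate and of being in a natural experiment, so the wording is too broad but the underlying point is sound.

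**What to change.** 1. In sections 3 and 3.2, state that later compulsory admission and OC are reported descriptively in WP1 and are not IV outcomes of earlier compulsion.
2. In sections 3.2 and 5.2, state that long-horizon IV or reduced-form results are read as the effect of sustained area practice, or of cumulative compulsory exposure over follow-up, and not of one episode.
3. In section 5.2, add that the no-contact control population cannot test the path through later decisions, and limit the blinding comparison to unawareness of the area's rate.

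The cost is wording, one outcome that loses its causal estimate, and a broader label on long-term results. No new data are needed. Restricting attribution to a short window after the first episode would also limit the problem, but it works against the project's stated long-term aim. It is a trade-off for the investigators and not part of this fix.

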**FIGURE 4 mpr1980-fig-0004:**
[figure not shown]
Trajectories observed in longitudinal registry data to be used in the project.

**FIGURE 5 mpr1980-fig-0005:**
[figure not shown]
Themes of outcomes and/or baseline characteristics, including potential operationalisation.

### WP1: The epidemiology of severe mental illness, compulsory hospitalisation, and outpatient commitment

3.1

This WP will answer three categories of epidemiological questions concerning people in contact with specialist mental health or addiction services in Norway in 2015–2016.

The first category will compare short and long‐term trajectories of persons with and without SMI in voluntary and compulsory care. Additionally, the outcomes of these persons will be compared to a control group from the general population.

The second category will describe the extent of geographical variation inPrevalence of SMI.All mental health service use for people with SMI, including referrals to specialist mental health care and per‐person use of antipsychotic medication.Compulsory inpatient and outpatient health service use.

We will test the competing hypotheses that providers who are less likely to use one form of compulsion may be more likely to use the other, or that providers who use little inpatient compulsion also tend to use little OC.

Data will be aggregated to geographical regions, specifically catchment areas to community mental health centres, based on residency. The variation will be described as population‐based rates and as the proportion of inpatients and outpatients with a compulsory referral or legal status. The relationship between urbanicity and risk of psychosis (Fett et al., 2019) has not previously been documented in Norway, but will also be covered in WP1.

The third category will explore associations between rates of compulsory care per population and indicators of social inequality and socio‐economic position in the catchment areas, such as the proportion of high school dropouts; median income in the area; and unemployment rate.

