### Geographical variation in compulsory mental health care: A source of concern and a toolbox for causal inference

2.5

Geographical variation in health services is more apparent in conditions where clinicians disagree about *‘right care’* (Wennberg, 2010). It is therefore unsurprising that geographical variation in compulsory hospitalisation is observed in all countries with available data: Belgium (Gedwongen verblijven in PZ en, 2021); Denmark (Engberg, 1991); England (Keown et al., 2016); Finland (The Finnish Institute for Health and Welfare, 2022); France (Gandré et al., 2018); Germany (Brieger et al., 2014); Ireland (Daly and Craig, 2021); Italy (Di Cesare et al., 2017); New Zealand (O’Brien et al., 2012); The Netherlands (Broer et al., 2020); South Korea (Hwang et al., 2020); Sweden (Statistikdatabaser, 2021); Switzerland (Schuler et al., 2018); and the United States of America (Lee and Cohen, 2021). Mental health services are expected to be of similar quality within most of these countries, and quality of care is not presumed to depend on area of residence.

Norway has a universal health care system where all residents are entitled to equal access to mental health care, and there is no separate private mental health sector. Still, after controlling for age and gender of residents, the average number of compulsorily hospitalised patients per person in the population in 2014–2018 was more than three times higher in the highest‐ranked area compared to the lowest (Hofstad et al., 2021), as illustrated on the right panel of Figure 3. Measured as the average number of days of compulsory hospitalisation per capita, the variation was more than eightfold. Compared to other European countries (Sheridan Rains et al., 2019), the average rate of compulsorily hospitalised patients in Norway is relatively high, as seen in the left panel of Figure 3.

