### Design

4.1

The project will use methods of description and causal inference (Hernán et al., 2019). Individual‐level data on the whole Norwegian population will be linked across multiple registries. If uncertainty remains whether conditions for IV‐analyses are met, the use of hierarchical models or inverse probability weighting might be relevant, in addition to conventional epidemiological approaches.

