### Study samples and target populations

5.1

Since the registers are mandatory, they typically contain data that is complete, reliable and representative. The project will obtain data on everyone above nine years who were referred to specialist mental health or addiction services in Norway 2015–2016. For WP1, we estimate that the patient sample and the equally sized control group from the general population will constitute approximately 600,000 individuals. For WP2 we will specify smaller target populations, with increased risk for compulsory mental health care. Relevant subgroups include people who have or will receive a diagnosis of SMI and people referred involuntarily during the study period.

The cohort period is limited to 2015–2016, but we will obtain data for both the cohort and control group for the period 2010–2025. This permits differentiation between the first episodes of SMI and patients with previous contact with specialist services.

The registry data will be supplemented with municipal data (See Table A1), which will be used to explore associations between structural and capacity‐related regional variables and rates of compulsory care and SMI. Furthermore, they can be used to adjust for different case‐mix in the catchment areas.

For both WPs it might be relevant to perform separate analyses for compulsory observation and compulsory mental health care, since the patient groups do not overlap completely and expected outcomes differ somewhat. Similarly, it can be relevant to perform subgroup analysis for some outcomes based on gender, diagnoses or other characteristics.

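### WP1 reports the extent of geographical variation as area rates and proportions, with no stated step to separate chance from real differences; the effect is small for compulsory hospitalisation and unknown for outpatient commitment

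*Protocol article*

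**What the plan says.** The relevant statements in the protocol article are these.

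- **Section 3.1 (WP1), aim.** "The second category will describe the extent of geographical variation" in three things: prevalence of severe mental illness (SMI), mental health service use, and compulsory inpatient and outpatient care.
- **Section 3.1, unit.** "Data will be aggregated to geographical regions, specifically catchment areas to community mental health centres, based on residency".
- **Section 3.1, summary measure.** The variation is to be described as population-based "rates and as the proportion of inpatients and outpatients with a compulsory referral or legal status".
- **Section 3.1, further use.** WP1 also tests whether the two forms of compulsion substitute for each other or whether "providers who use little inpatient compulsion also tend to use little OC".
- **Section 5.1.** "The cohort period is limited to" 2015–2016. Municipal data may be used to adjust for case mix.
- **Section 5.2.** More than 80% of the variation in ranked population rates of compulsory hospitalisation was predictable from the previous year, while 50–75% "of variation in inpatient rates could be predicted this way". Nothing comparable is given for OC.
- **Section 4.1 (Design).** If doubt remains about the instrumental-variable (IV) conditions, "the use of hierarchical models or inverse probability weighting might be relevant".

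The article gives neither the number of catchment areas nor the number of events per area.

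**The concern.** Suppose every catchment had exactly the same underlying rate. Observed rates would still differ by chance, and more so where counts are low. A description that rests on observed rates and proportions therefore reports real practice differences and sampling noise together. The only modelling approach in the article that would separate them, hierarchical models, is tied in section 4.1 to doubt about the IV conditions and not to the WP1 description. Case-mix adjustment deals with a different problem and does not remove sampling noise.

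At stake is how WP1's second category will be read. It lists SMI prevalence, service use, inpatient compulsion and OC together. A reader who sets their spreads side by side would find the rarer measures more variable through chance alone. If the same observed rates feed the test of inpatient against OC use, noise would also pull that association towards zero.

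**Working it through.** WP1 states no variance component or expected spread, so there is no plan figure to reproduce. Two checks are possible.

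**1. Compulsory hospitalisation, from section 5.2.**

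Inputs: previous-year R² of 0.80 (the stated lower limit) for ranked population rates, and 0.75 to 0.50 for inpatient rates. Assumptions: rank predictability stands in for predictability of the rates, and all non-persistence is chance. The second gives an upper limit, because real year-to-year change also lowers R².

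Formulas: one-year reliability r = √R²; two-year reliability by Spearman–Brown, r₂ = 2r/(1 + r); chance share = 1 − reliability; SD overstatement = 1/√reliability − 1.

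| Measure | R² | r | chance share, 1 year | r₂ | chance share, 2 years | SD overstated, 2 years |
|---|---|---|---|---|---|---|
| Population rates | 0.80 | 0.894 | 11% | 0.944 | 6% | 3% |
| Inpatient rates | 0.75 | 0.866 | 13% | 0.928 | 7% | 4% |
| Inpatient rates | 0.50 | 0.707 | 29% | 0.828 | 17% | 10% |

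The two-year column is the relevant one, because the cohort spans two years.

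**2. OC, under assumed counts.**

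For Poisson counts with mean μ per area of equal size, observed CV² = true CV² + 1/μ. The chance share of the observed variance is (1/μ)/(1/μ + CV²), and the SD is overstated by √(1 + 1/(μ·CV²)) − 1. With an assumed true CV of 0.25, CV² = 0.0625.

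- μ = 10: 0.1/(0.1 + 0.0625) = 62%; SD overstated by √2.6 − 1 = 61%.
- μ = 100: 0.01/(0.01 + 0.0625) = 14%; SD overstated by √1.16 − 1 = 8%.
- μ = 400: 0.0025/(0.0025 + 0.0625) = 4%; SD overstated by √1.04 − 1 = 2%.

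The answer thus runs from serious to negligible, depending on a count that the article does not give.

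**3. Which summary recovers the true spread.**

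This was simulated with 70 equal areas (assumed), true CV 0.25 and 4,000 replicates. The median true highest/lowest ratio is 3.2. From observed rates it is about 9 at μ = 10 and 4.5 at μ = 30, which is too large. From shrunken (empirical Bayes) rates it is about 2.0 and 2.55, which is too small. Neither set of extremes estimates the true spread. The between-area variance from a random-intercept model targets it directly.

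**The case against.** The strongest case on the other side has four parts.

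*Section 3.1 names denominators and not an estimator.* This stands in part. The article does not call the rates raw and does not exclude adjustment, intervals or random effects, and a fuller plan may specify them. A reader might infer that the authors have chosen unadjusted rates and rejected modelling; the text does not support that. What it does state is the form in which the extent of variation will be described, and a better form is available at little cost.

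*The authors already plan to look at chance.* Section 5.2 lists, among topics to investigate, whether the variation is random or stable over time. It does so in support of the IV assumptions, and it does not change how WP1 reports the extent of variation.

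*Highest-to-lowest ratios are not a WP1 method.* This stands. A reader might infer from section 2.5 ("Measured as the average number of days of compulsory hospitalisation per capita, the variation was more than eightfold") that WP1 will report such ratios and that chance will inflate them several-fold. Those figures are background from earlier published work, and section 3.1 plans no such ratio.

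*Hospitalisation rates are stable.* This also stands. It is tempting to cite only the 50–75% figure as proof of heavy noise. The same sentence in section 5.2 gives more than 80% for population rates, the first measure that WP1 names, and unpredicted variation is not all chance.

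**Conclusion.** The point holds in a limited form. WP1's stated summary mixes real and chance variation, and a between-area variance with an interval would be a better measure of extent.

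For compulsory hospitalisation the consequence is small: at most about 3% on the two-year SD for population rates and 4–10% for inpatient rates. These figures treat ranks as a stand-in for rates and all non-persistence as chance.

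For OC the size cannot be derived from the article. The chance shares of 62%, 14% and 4% rest on assumed mean counts of 10, 100 and 400 and an assumed true CV of 0.25. They show that the matter needs settling and do not show that OC variation will be badly overstated.

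A reader might go further and infer that the geographical-lottery argument or WP2 is undermined. The article does not support that. The lottery argument draws on earlier published variation, and WP2 relies on instrument relevance, for which section 5.2 cites year-to-year stability of hospitalisation rates.

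**What to change.** In section 3.1, for each measure in the second category and above all for OC:

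- Fit a Poisson model with a population offset (rates) or a binomial model (proportions), with a random intercept for catchment area.
- Report the between-area SD, or the median rate ratio (median odds ratio for proportions), with its interval as the extent of variation.
- Show the observed area rates and proportions beside it, with intervals.
- Do not take highest-to-lowest ratios from shrunken area rates, because these understate the true spread.

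The cost is one standard model per measure on data already planned, and a somewhat smaller reported spread. Where counts are large the result will barely move, and the claim of real variation is then better supported.
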